### Study Procedure

All participants will be recruited from the abovementioned universities via advertisements on online bulletin boards, campus newspapers, and posters. Interested students who contact the researchers via email will be provided with further information related to the study and will be given time to consider their participation. If interested, they will be screened using Google forms (developed by the authors for this study) for eligibility using the Japanese version of the CES-D [30]. The cutoff score of CES-D was verified in Japanese samples [30]. If the score is 16-24, the researcher will continue with the eligibility interview to confirm that all other criteria are met. At the end of the interview, written consent will be obtained. Those who score less than 15 or above 25 will be excluded from the trial but will be provided with free access to SPARX, according to the needs of the participant. Those whose score is 25 or more, indicating severe depressive symptoms [31,32], will be provided with information about available mental health care services.

For participants in the treatment condition, SPARX will be delivered on their mobile phone or tablet device. They will be asked to play the SPARX program weekly at a designated university location (eg, a vacant laboratory or conference room) with one of the researchers (or a research assistant) present in another room (eg, a neighboring laboratory) for the purpose of checking SPARX use and being available to answer any questions from the participant. Each weekly session with SPARX is expected to take about 30 min.

Participants in the wait-list condition group will receive access to SPARX after a 1-month follow-up assessment of the treatment condition group. They will be asked to fill out assessments at the same time as the assessments of the treatment condition group at experimental laboratories, in conference rooms at each university, or on online Google forms. They will not be granted access to SPARX until all assessments have been completed.

To address potential issues of contamination, we forbid participants from talking about any theme of SPARX, such as the use of SPARX and any impressions of this study, during trial participation because other students in their university campus are participating in the current trial.

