Participants will be excluded if they have: (1) high risk of self-harm or suicide at study entry based on a self-report; (2) severe depressive symptoms, as indicated by a CES-D score>24 [31,32]; (3) current manic episodes or current schizophrenia or other psychotic disorders at baseline as reported by a participant; (4) previous experience of using SPARX; and (5) involvement in manualized psychotherapy at baseline. These exclusion criteria are the same as those adopted in the first SPARX study [26] as reference. Merry et al [26] suggested that people exhibiting severe depressive symptoms or at high risk of self-harm or suicide should be excluded because they could not provide a self-help resource as a viable option. In addition, individuals experiencing current manic episodes, schizophrenia, or other psychotic disorders, or are involved in manualized psychotherapy at baseline were excluded because they require medical and psychiatric treatment suitable for their symptoms rather than SPARX or are already receiving suitable psychiatric treatment. If we do not reach the sample size required to test the primary hypothesis of this study, we will extend recruitment to other interested universities and will consider using online recruitment.

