### Clinical Safety Procedures

For participants indicating a high risk of self-harm or suicide at screening and at any time during this trial, the researchers will provide information on available mental health care services that the participants can access and will ask the participant to cease participation in this trial. However, participants will be provided with ongoing access to SPARX even if they decide to withdraw from the trial. In relation to ancillary care, the participants will be allowed to contact the researchers at any point during the trial. If any event requiring additional care occurs, a researcher will inform the individual at the contact address or telephone number of the appropriate medical or psychological care and mental health service as provided by the participant’s health insurance.

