### Wait-List Control

Participants randomized to the control group will be placed on a wait list for 11 weeks; that is, until after the 1-month follow-up assessment of the group assigned to the intervention. The participants on the wait list will then be offered the opportunity to take part in the SPARX program in the same way as those in the intervention group.

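### Students screened out on the CES-D are offered SPARX without reaching the interview where mania and psychosis are asked about

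*Protocol article*

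**What the plan says.** All places are in the protocol article.

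- **Screening (Study Procedure).** Interested students first complete an online form: "they will be screened using Google forms (developed by the authors for this study) for eligibility using the Japanese version of the CES-D". The next step depends on the score: "If the score is 16-24, the researcher will continue with the eligibility interview to confirm that all other criteria are met". Written consent comes at the end of that interview.
- **Outside the window (Study Procedure).** Scores under 15 are handled in the same sentence as high ones: students "above 25 will be excluded from the trial but will be provided with free access to SPARX, according to the needs of the participant". In addition, anyone scoring 25 or more "will be provided with information about available mental health care services". No start date is given for access outside the trial.
- **Reasons for exclusion (Participants).** People with current mania or psychosis, or in manualized psychotherapy, are excluded "because they require medical and psychiatric treatment suitable for their symptoms rather than SPARX", or because they already receive suitable care. For severe symptoms or high risk of self-harm, the section relies on the first SPARX study, which did not regard a self-help resource as viable for such people.
- **Self-harm risk (Clinical Safety Procedures).** "For participants indicating a high risk of self-harm or suicide at screening and at any time during this trial", researchers give information on services and ask the person to stop taking part. Access to SPARX continues for those who withdraw.
- **Contamination (Study Procedure).** Participants may not talk about SPARX "during trial participation because other students in their university campus are participating in the current trial".

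**The concern.** The protocol gives clinical reasons why certain people should not rely on SPARX, and it finds those people by asking them at interview. It then offers the same app to students who are turned away before that interview. Some of them have the most severe symptoms of anyone screened. A student with a high score and a current manic or psychotic episode could be given SPARX with no stated question that would reveal it. A milder student applying for the trial would be asked.

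What is at stake is the safety of people outside the randomized comparison. A lesser matter concerns the trial itself. Screened-out students may hold the app on the same campuses as the wait list, and the rule against discussing SPARX is not clearly addressed to them.

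**Working it through.** The plan gives no figure on this point, so the check sets its sections side by side.

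**1. What happens at each score.** Inputs: the inclusion range of 16-24 and the exclusion above 24 (Participants), and the routing rules (Study Procedure).

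| CES-D score | In the trial? | Interview? | SPARX offered outside the trial? | Service information on score alone? |
|---|---|---|---|---|
| Below 15 | No | No | Yes, by need | No |
| 15 | No | No | Not stated | No |
| 16-24 | If all other criteria are met | Yes | Not applicable | No |
| 25 | No | No | Not stated | Yes |
| Above 25 | No | No | Yes, by need | Yes |

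Two things follow. Both groups offered the app miss the interview, low scorers as well as high scorers. And scores of 15 and 25 are ineligible but fall outside the sentence that makes the offer.

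**2. Where each reason for unsuitability is checked.**

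- *Mania or psychosis (criterion 3).* This is self-reported and belongs to the other criteria confirmed at interview. The online screen is described as using the CES-D. No other step is stated, so it is not checked for anyone outside 16-24.
- *High risk of self-harm or suicide (criterion 1).* This is also self-reported. Clinical Safety Procedures gives a response at screening, so it is partly covered. How the risk would be noticed in a student who is not interviewed is not stated, and access to SPARX does not depend on it.
- *Severe symptoms (criterion 2).* The score itself reveals these. The stated response is service information, given alongside the offer of SPARX and not as a condition of it. Nothing tells the student that SPARX does not replace those services.

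**3. Offer against reasons.** The offer turns on need. The Participants section's reasons turn on suitability: other treatment in place of SPARX for mania and psychosis, and doubt about self-help for severe symptoms or high risk. A student can need help and still be someone for whom the protocol considers SPARX the wrong help. Following the stated rule exactly would not separate the two.

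**4. The no-discussion rule.** It is addressed to participants while they take part in the trial. Screened-out students are excluded and do not reach the consent step. On the other hand, the offer sentence itself calls a screened-out student a participant, so the rule's reach is unclear. The setting is three universities, recruitment from April 2019 through March 2020, and this wait: "Participants randomized to the control group will be placed on a wait list for 11 weeks". If access starts at screening, it can fall within those waits.

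**5. Effect on the plan's numbers.** None. For reference, the sample size reproduces. With a standardized effect of 0.60, two-sided alpha 0.05 and power 0.80, a two-sample t-test needs 44.6 per arm, so 45 per arm and 2 × 45 = 90 in total (power 0.804). Allowing for 10% dropout gives 90 / 0.9 = 100. Nothing in this point enters that calculation.

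**The case against.** The strongest reply is that this is a condensed article. How staff decide on access outside the trial is operational detail that a fuller protocol or site procedure may hold. The offer is not unconditional, because it depends on need, which may imply judgement case by case. Three review boards approved the study. The Participants section explains trial exclusions; it does not call SPARX harmful. Clinical Safety Procedures shows that eligibility and app access are kept apart on purpose, since people who withdraw keep the app.

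Much of this stands. It limits the point in four ways.

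- A reader might infer that SPARX is contraindicated in mania or psychosis. The documents say only that other treatment is needed in its place.
- A reader might infer that high scorers get no safeguard at all. They get service information on score alone, and self-harm risk at screening has a stated response.
- A reader might infer that students at high risk of self-harm should be refused the app. That would clash with the continuing access in Clinical Safety Procedures.
- A reader might infer that contamination will cost power, or that the no-discussion rule plainly excludes these students. The article gives neither the share exposed nor the timing of access, and it uses the word participant loosely. Hearing about an app is also not the same as receiving seven modules.

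What the reply does not remove is the conflict between two things the article does state: a rule for giving access, and reasons for unsuitability that the rule does not consult. That is more than silence on a detail.

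**Conclusion.** The point holds in a limited form. The Study Procedure section offers SPARX to screened-out students at both ends of the scale without the question on mania and psychosis that trial entrants are asked. For high scorers, it does so despite the protocol's own doubt about self-help for severe symptoms.

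The number of students affected is not in the article and cannot be derived from it. The contamination route is possible but of unknown size, and no loss of power is claimed. The conclusion assumes that the article describes the screening path as it is carried out; a site procedure that already asks these questions would answer the safety part. Priority is minor, because the point concerns people outside the trial and changes no endpoint, sample size or analysis.

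**What to change.** Replace the sentence in Study Procedure that makes the offer with text to this effect:

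> Students scoring 15 or less, or 25 or more, are excluded from the trial. Before any of them is given SPARX, the researcher asks the self-report questions used for exclusion criteria 1 and 3. A student reporting current mania or psychosis is directed to services instead of SPARX. A student reporting high risk of self-harm or suicide first receives information on services, and SPARX is offered only as an adjunct to that care. Students scoring 25 or more are told that SPARX is not a substitute for the services listed. Otherwise SPARX may be given according to need.

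Keep the following sentence on service information for scores of 25 or more. The Participants and Clinical Safety Procedures sections need no change, because treating SPARX as an adjunct fits the continuing access already stated there. The new score limits also settle where 15 and 25 belong.

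As a minor addition, ask students given the app not to discuss SPARX with other students on campus while the trial runs there, with talk to clinicians and family exempt. For people outside the trial this is a request that rests on goodwill.

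The cost is a few self-report questions for each screened-out student who wants the app, and a small amendment at the three review boards while enrollment is under way (the Results section reports 60 recruited).

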### Ethics

This study protocol was reviewed and approved by the institutional review board of Hokusho University (2017-021; February 20, 2018), Ritsumeikan University (2018-028; September 19, 2018), and Health Sciences University of Hokkaido (18-006, December 8, 2018). Furthermore, this study has been registered with UMIN (000034354). Details of this trial will be explained by the researchers to the participants before study participation. Written informed consent will be obtained from participants prior to entering them into the trial. All outcome data, including written informed consent, will be securely stored at the participating university (eg, Ritsumeikan University) in a locked cabinet. All identifying information will be removed, and the participants will only be identified by a unique participant number.

### Randomization

Participants (N=100) who fulfil all eligibility criteria will be randomized at a 1:1 ratio to either the SPARX intervention group or the wait-list control condition. The randomization sequence will be generated by the trial statistician and stratified by site. The final randomization lists will be computer-generated and concealed in a secure study database until the end of data collection/data lock.

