### Setting

This multicenter study will be conducted at three universities: Health Sciences University of Hokkaido, Hokusho University, and Ritsumeikan University. We plan to recruit participants from April 2019 through March 2020.

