### Sample Size

A meta-analysis of RCTs examining the effects of CBT in comparison to wait-list on depression in university students showed an effect size of 1.13 [34]. However, the effect sizes were smaller (0.56 [35] and 0.64 [36]) for studies in adults compared to those of internet-based and other computerized psychological treatments with wait lists. A meta-analysis of RCTs to examine the effectiveness of game-based digital interventions showed an overall effect size of 0.66 (against a wait-list control condition), 0.47 (with a target population of adolescent users), and 0.41 (type of game: psychoeducation and training, including the SPARX study) [22]. Additionally, a meta-analysis of RCTs to examine the effectiveness of technology-delivered interventions for depression and anxiety in children and adolescents showed an effect size of 0.45 compared to the wait-list group [37]. Considering these findings, we assumed a similar effect size (0.60) to that of internet-based and other computerized psychological treatments or game-based digital interventions against wait-list [22,35,36] for the reduction of primary outcomes assessed using Patient Health Questionnaire-9 (PHQ-9).

A power analysis showed that a target sample size of 90 was needed to detect an effect size of 0.60 with alpha=.05 and a power of 0.80 for a two-tailed test. Considering an anticipated 10% dropout [38], we will aim to recruit at least 100 (50 per group) participants to test the primary hypothesis of this study.

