### Statistical Analyses

The analysis for primary outcome measures will be conducted using a linear mixed model (LMM). The LMM approach was selected because of its strength in accommodating missing data and its ability to incorporate random effects into analyses. In these analyses, the dependent variable is the PHQ-9 score, and the independent variables are assignment (treatment condition, wait-list condition) and time [preassessment (T1), each session assessment (T2-T7), post-assessment (T8), and follow-up assessment (T9)], with interaction of the assignment and time as fixed-effect variables and participants as a random-effects variable. Secondary outcomes (outcome measures, process measures, and evaluation of the program) will be analyzed in the same way as the primary outcome. Subgroup analyses are not planned. For all analyses, *P*<.05 will be inferred as statistically significant. Up-to-date versions of R software (R Foundation for Statistical Computing, Vienna, Austria) will be used to analyze the quantitative data.

In the satisfaction/acceptability measure, free comments will be analyzed using thematic analysis.

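### Randomisation is stratified by site but the stated mixed model has no site term; the loss of precision is small, conservative, and depends on the contrast tested

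*Protocol article*

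**What the plan says.** On design, Setting states that "This multicenter study will be conducted at three universities". Under Randomization, 100 eligible students "will be randomized at a 1:1 ratio to either the SPARX intervention group or the wait-list control condition", and "The randomization sequence will be generated by the trial statistician and stratified by site". Site is the only stratification factor named.

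On analysis, Statistical Analyses states the model: "the dependent variable is the PHQ-9 score, and the independent variables are assignment (treatment condition, wait-list condition) and time", "with interaction of the assignment and time as fixed-effect variables and participants as a random-effects variable". Time runs over T1 (baseline), T2 to T7, T8 and T9, so baseline PHQ-9 is one of nine repeated responses. Secondary outcomes are to be handled in the same way. Site appears among neither the fixed nor the random effects.

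Two further statements bear on the size of the problem. The section does not say which contrast from the model is the primary test, while Results describes the primary outcome as depressive symptoms at the 1-month follow-up. Participants allows further universities to be added if recruitment falls short.

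**The concern.** Stratified allocation balances the arms within each university, which removes between-site variation from the true sampling error of a between-arm comparison. If the model does not know about site, its estimated error for such a comparison still contains that variation. The reported standard error is then larger than the true one, the test is conservative, and the precision gained by stratifying is not used.

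The stake is a little power and a mismatch between how the trial was randomised and how it is analysed. The question is how far this mechanism reaches into the model as written, where each participant supplies a baseline response.

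**Working it through.** **Inputs from the article.** Effect size 0.60, two-sided alpha 0.05, power 0.80, target 90, 10% dropout, 100 recruited (Sample Size); three sites (Setting); 1:1 allocation stratified by site (Randomization); nine assessments (Measures). The between-site share of PHQ-9 variance is not given, so every share below is an assumption.

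**The plan's own figure.** An exact two-sample t test with 45 per arm at d = 0.60 has power 0.804, so 90 reproduces, and 90/0.90 = 100. The sample size does not depend on this point. The normal approximation used below gives 0.812 for the same case.

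**Arm difference at a single time point.** With site share s, the reported SE divided by the true SE is 1/sqrt(1 − s). The formulas are:

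- Type I error without site: 2[1 − Φ(1.96/sqrt(1 − s))].
- Signal: 0.60/sqrt(2/45) = 2.846.
- Power without site: Φ((2.846 − 1.96)/sqrt(1 − s)).
- Power with site: Φ(2.846/sqrt(1 − s) − 1.96).

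| Assumed share s | SE ratio | Type I error, no site | Power, no site | Power, with site |
|---|---|---|---|---|
| 0 | 1.000 | 0.050 | 0.812 | 0.812 |
| 0.01 | 1.005 | 0.049 | 0.813 | 0.816 |
| 0.05 | 1.026 | 0.044 | 0.818 | 0.832 |
| 0.10 | 1.054 | 0.039 | 0.825 | 0.851 |
| 0.20 | 1.118 | 0.028 | 0.839 | 0.889 |

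For 5% to 10%, the SE is 2.6% to 5.4% too wide. In participants that is s × 90 = 4.5 to 9.

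**Assignment-by-time change contrast.** Write the outcome as site shift + participant intercept + time and treatment terms + residual. In change from T1 to T8, any site shift that is constant over time subtracts out. A REML random-intercept simulation (N = 100, three sites, nine time points, 300 replicates per scenario) gives these mean standard errors for the T1-to-T8 contrast:

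| Assumed site share | Assumed site-by-time share | Dropout | No site | Site | Site + site-by-time |
|---|---|---|---|---|---|
| 0.05 | 0 | 0% | 0.1787 | 0.1787 | 0.1787 |
| 0.05 | 0 | 10% | 0.1833 | 0.1833 | 0.1834 |
| 0.10 | 0 | 10% | 0.1836 | 0.1836 | 0.1836 |
| 0.20 | 0 | 10% | 0.1833 | 0.1833 | 0.1834 |
| 0.10 | 0.10 | 10% | 0.1870 | 0.1870 | 0.1845 |

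With a constant site shift, omitting site costs nothing to within about 0.0001. Only the last row shows a loss, and a site main effect does not recover it. Site-by-time does: 1 − 0.1845/0.1870 = 1.3%.

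**Cross-check.** In the same runs, the assignment coefficient is the arm difference at T1, a single-time-point comparison. With 10% dropout its SE falls from 0.1991 to 0.1941 (share 0.05), 0.2006 to 0.1903 (0.10) and 0.2002 to 0.1790 (0.20) when site is added. The ratios 1.026, 1.054 and 1.118 match the formula.

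**Parameter count for the fix.** With time categorical, the stated model has 1 + 8 + 1 + 8 = 18 fixed effects. Site adds 3 − 1 = 2, and site-by-time adds (3 − 1)(9 − 1) = 16. The total added is 18.

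**The case against.** The strongest reply is that the model already protects the contrast that matters. Baseline is a response, so the treatment effect on change is carried by assignment-by-time, where a constant site difference has no effect. This stands for that contrast. It does not cover an arm difference at the 1-month follow-up, which is how Results frames the primary outcome. Nor does it cover satisfaction, which is scheduled only at T9 and has no baseline from which a site difference could cancel.

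A second reply is that this is a condensed article and adjustment for strata often sits in the SAP. That is fair as a caution: the unseen SAP may already include site, and nothing in the article says that site will be excluded. But the article does not leave the model open. It lists the fixed and random effects, and the only stratification factor is not among them.

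A reader might also infer more than the documents support:

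- **That standard errors are too wide for the treatment effect in general.** They are not for the change contrast unless sites differ in their course over time. The 2.6% to 5.4% and the 4.5 to 9 participants belong to between-participant comparisons only.
- **That only 45 per arm will be analysed.** That figure is half of the 90 in Sample Size. The mixed model keeps participants with partial data.
- **That the omission risks a false positive.** The error runs the other way.
- **That the remedy is one free term.** A site main effect alone does nothing for change contrasts, and the version that does help adds up to 18 parameters.

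**Conclusion.** The point holds as a mismatch between design and analysis: site defines the randomisation strata and is absent from the stated model.

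Its effect is small and conservative. For a single-time-point arm difference, the standard error is 2.6% to 5.4% too wide, and power is lower by about 1.3 points (0.818 against 0.832) to 2.6 points (0.825 against 0.851). This assumes that site explains 5% to 10% of PHQ-9 variance. For the assignment-by-time contrast the loss is nil under a constant site difference, and about 1.3% if site and site-by-time each carry an assumed 10% share. If sites do not differ at all, nothing is lost.

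Different courses by site are plausible, since sessions are held on each campus with local staff nearby, but the article gives no data on it. The omission itself is certain from the text. The size of its effect cannot be computed from the article.

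**What to change.** In Statistical Analyses, add site as a fixed effect to the primary and secondary models, and add site-by-time wherever the contrast is a change over time. For an outcome measured only at T9, the site main effect is enough. Fix in advance a rule for pooling very small sites, in case universities are added as Participants allows.

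Do not enter baseline PHQ-9 as a covariate while T1 remains in the outcome vector, because the same measurement would then sit on both sides of the model.

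The cost is up to 18 further fixed-effect parameters in the primary model, which doubles the 18 it has now if time is categorical, for 100 participants; added universities would raise this. Secondary outcomes measured at T1, T8 and T9 would need 2 + (2 × 2) = 6. No data collection changes. Results reports enrolment as ongoing with analysis to follow completion, so on that account the model can be amended before analysis.
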